#### **Simulated cost effectiveness analysis:**

The cost-effectiveness of the Heart Matters campaign will be assessed using a simulation model. Health sector costs and disability adjusted life years (DALYs) avoided before and after the delivery of the intervention will be estimated. If appropriate, the incremental cost per DALY avoided from the Heart Matters campaign compared to usual care will be estimated.

Where estimates of resource use are derived from the study, these estimates will be obtained by using mixed-effects logistic regression analysis consistent with that conducted for the primary and secondary outcomes of this study.

Since the primary health benefit is expected to be from the treatment of ACS, disability adjusted life years (DALYs) avoided will be estimated based on improvements in numbers of patients treated after ACS and improvements in the numbers of patients treated within the first 90 minutes of symptom onset. This outcome will be estimated using information from the published literature and project data.

One-way and multivariable probabilistic sensitivity analyses will be conducted whereby model inputs are varied in order to test robustness of cost-effectiveness estimates. Where relevant, we will also draw on advice set out for economic modelling in the Australian government Technical Guidelines for preparing assessment reports for the Medical Services Advisory Committee and guidelines for undertaking health economic evaluation alongside stepped wedge trials.

The steering committee will be involved in the decisions made for modelling assumptions and the best sources of evidence for this sub-study where these are unable to be obtained from the study data.

## **DATA MANAGEMENT**

### **Data entry**

Research Electronic Data Capture (REDCap) will be used for capturing Heart Matters session (e.g. anonymous surveys and session information) data. REDCap is a secure web application that is widely used for building and managing surveys and online databases. It has an intuitive interface for validated data entry, audit trails for tracking data manipulation and export procedures and allows for seamless downloads of collected data to common statistical packages.

### **Security and storage**

All data collected externally will be de-identified by data custodians and electronically sent to Monash University investigators fully de-identified via the Secure File Transfer Protocol (SFTP). VCOR data will be accessed by the statistician for analysis via the VCOR Secure eResearch Platform (SeRP). All data will be kept on a secure password protected server at Monash University maintaining confidentiality in accordance with local legislation. Access to the data will be restricted to CIA, the study coordinator and statistician.

Monash University implements a defence in depth approach to information security and employs a multitude of controls to protect its infrastructure and data. These controls are

regularly audited to ensure they meet global best practices and are aligned with ISO 27001 security practices. Data collected will be stored on University managed secure and resilient infrastructure located in Australia that complies with all applicable data protection and privacy obligations.

#### Retention and archiving

The study team will retain all study records in a safe and secure location for a minimum of 7 years after the completion of the study in accordance with Australian and Victorian legislation. (*The Australian Code, which asks for a minimum of 5 years from publication date and the Victorian Health Records Act of health information for 7 years*).

## ETHICS AND DISSEMINATION

#### Ethical conduct of the study

The study will be conducted in accordance with all relevant ethical and regulatory approvals and guidelines set by the National Health and Medical Research Council of Australia, the Declaration of Helsinki, its subsequent amendments, and the ICH-GCP guidelines on the ethical conduct of research. A Human Research Ethics Committee registered with the NHMRC will review the protocol prior to commencement of the study.

#### Protocol amendments

The steering committee will review and approve all protocol amendments. The lead HREC will review any protocol amendments prior to implementing any protocol changes.

#### Consent

##### *Waiver of consent*

A waiver of informed consent is requested from the overseeing HREC to deliver the heart health education campaign and use de-identified data sets from DHHS (VEMD and VAED), Ambulance Victoria (VACAR, VASQI and calls to ambulance), Monash University (VCOR), Medicare (Heart Health check numbers by LGA) and the Heart Foundation (Heart Watch survey data).

The Heart matters study is a cluster-randomised trial where the intervention is delivered at the cluster level (i.e. each Local Government Area). With nearly 1.8 million residents across the eight LGA's it is not feasible to obtain informed consent for every individual member of the cluster exposed to the intervention.

The use of de-identified data sets meets the requirements set out in chapter 2.3 of the National statement for a waiver of consent. The use of data sets from DHHS (VEMD and VAED), Ambulance Victoria (VACAR, VASQI and calls to ambulance), Monash University (VCOR), Medicare (Heart Health check numbers by LGA) and the Heart Foundation (Heart Watch survey data) is routinely collected and de-identified therefore posing a low risk and it

is impractical to obtain consent for data that has already been collected. There is sufficient protection of participant privacy as all data sets will be de-identified and investigators will not attempt to re-identify cases.

#### *Implied consent*

The anonymised data collected from education evaluation surveys will be collected under implied consent. Completion of the survey will be considered as implied consent.

#### **Confidentiality**

The study team will take every precaution to ensure privacy and confidentiality in accordance with local legislation on privacy and the use of health data. As such, only researchers directly involved in the study will have access to patient data. De-identified data will be entered into the database and only aggregate data will be reported and published.

#### **Dissemination and authorship**

Study protocol, economic and statistical analysis plans will be published in a peer-review journal and prior to trial commencement. The trial will be registered on clinical trials.org.

Trial results will be communicated by publication (e.g. medical journal articles, media releases, website and social media) and presentations (e.g. scientific conferences, stakeholder presentations).

#### *Authorship eligibility guidelines*

Authorship will be granted to all chief and associate investigators who meet the ICMJE guidelines and maintain a role in the study throughout its duration.

The ICMJE recommends that authorship be based on the following four criteria:

1. Substantial contributions to the conception or design of the work; or the acquisition, analysis, or interpretation of the data for the work; AND
2. Drafting the work or revising it critically for important intellectual content; AND
3. Final approval of the version to be published; AND
4. Agreement to be accountable for all aspects of the work in ensuring that questions related to the accuracy or integrity of any part of the work are appropriately investigated and resolved.

Those who contribute to the study but do not meet all four criteria for authorship will be listed in an acknowledgements section within the publication.

#### **COVID-19 Planning**

In March 2020, Victoria was declared a state of emergency due to COVID-19 and in July 2020 a state of disaster was declared. During this time, Victoria has been under stage 3 and stage 4 restrictions where there are only four reasons to leave home; shopping for essentials, medical treatment, work and education (if permitted) and exercise (two person limit). With

such restrictions in place, planned Heart Matters interventions such as the launch events and face-to-face sessions with community groups cannot take place. For this reason, the intervention phase has been postponed to April 2021 in the hope that restrictions will have eased by that time. If restrictions are still in place, the intervention will be delivered in a digital format. Where restrictions have eased but social distancing can be applied, the intervention will be adapted to fit these requirement, i.e. small groups outdoors.

## STUDY TIMELINES

| Time period                                         | Actions                                                                                                                                                                                                                                                          |
|-----------------------------------------------------|------------------------------------------------------------------------------------------------------------------------------------------------------------------------------------------------------------------------------------------------------------------|
| Planning Phase
April 2020 –February 2021  | Protocol Development
Ethics application
Intervention refinement
Evaluation refinement
Employ staff
Gather and develop education materials
Gather and develop evaluation materials
Publications: background and protocol
Publication plan |
| Intervention Phase
April 2021- March 2023 | Intervention
Data collection (hospital and evaluation)
Publications: statistical plan and economic evaluation plan                                                                                                                                         |
| Evaluation Phase
July 2022- December 2024 | Data collection (major datasets) and analysis
Publications: main study, sub-studies.
Reporting                                                                                                                                                             |

## **APPENDICES**

### Daily Activity reports HM coordinators

- Date
- Location of presentation
- Number of attendees at presentation
- Materials used
- Presentation type
- Any key barriers to this session?
- Any key facilitators to this session?

[figure not shown]

**Heart Matters: A stepped wedge cluster randomised trial to test the effectiveness of heart health education in regions at highest-risk**

## 1 Administrative information

### 1.1 Study identifiers

- Protocol Number: 1.0 (MUHREC: 2020-26296-52553)
- Published protocol reference: [name], [name], [name], [name], [name], [name], [name], [name], [name], [name], [name], [name], [name], [name], [name], [name], [name], [name], [name], [name]. A protocol for the Heart Matters Stepped wedge cluster randomised trial: the effectiveness of heart attack education in regions at highest risk. Resus Plus 2023;15:100431
- ClinicalTrials.gov register Identifier: NCT04995900

### 1.2 Revision history

| Version           | Date          | Details                                                                                                              |
|-------------------|---------------|----------------------------------------------------------------------------------------------------------------------|
| 0.1 (first draft) | 23 May 2023   | First full draft by [name] (JK); sent to [name] (JB) for input and addition of non-statistical components |
| 1.0               | December 2023 | Incorporation of comments from JB and JK; input from RB.                                                             |
| 1.1               | March 2024    | Incorporation of further comments from JB, JK, RB, [name] and [name]                                      |

## 2 Introduction

---

### 2.1 Brief background and rationale

A detailed background is given in the protocol publication.[1] Briefly, reperfusion therapies in acute coronary syndrome (ACS) significantly improve survival rates, particularly when administered promptly.[2, 3] However, patient delay in recognising ACS symptoms and seeking timely medical attention remains a major obstacle to achieving optimal outcomes.[4] Public education campaigns, including mass media initiatives, have shown positive results in increasing ACS awareness and encouraging individuals to promptly contact emergency medical services (EMS) for early treatment.[5, 6] However, sustained exposure to these campaigns is necessary for their long-term effectiveness, and their high cost may not be sustainable.[7] Therefore, an alternative approach is suggested, which involves targeting regions with known high rates of ACS and low EMS use for ACS.

To address this gap in evidence, the Heart Matters trial was established. The trial aims to investigate the impact of community-level education, providing information on ACS risk factors and symptoms, while addressing the known barriers to calling EMS. This trial builds upon previous community-based trials, such as the REACT study,[8] by specifically focusing on regions with high rates and risk of ACS, as well as low EMS use for ACS.

### 2.2 Study setting and LGA selection

The National Heart Foundation of Australia's Victorian Heart Maps were used to identify areas with high rates of ACS. A comprehensive analysis of 32 local government areas (LGAs) in Victoria with high and low rates of acute myocardial infarction (AMI) revealed distinct characteristics in regions with the highest rates. These characteristics included lower education levels, socio-economic disadvantage, higher rates of cardiovascular risk factors, elevated prevalence of other cardiovascular conditions, lower cardiovascular knowledge, and a lower likelihood of using EMS for ACS.[9]

The Heart Matters intervention was implemented in eight of these high-risk LGAs in the Australian state of Victoria. The eight LGAs represent approximately 28% (n=1.8 million) of the state's population. Four LGAs are located in metropolitan Melbourne, including one in the inner city and three on the outskirts. The remaining four LGAs are in rural locations. The final selection of these eight LGAs considered the sample size requirements[10], estimated budget and geographical distance of LGAs to prevent contamination between intervention and control areas.

## 2.3 Eligibility criteria

The educational intervention was available to all adult community members in the selected LGAs. To enhance engagement and delivery, where possible, the Heart Matters Coordinators focused on specific sub-groups and postcodes (priority postcodes) within each LGA that had known low ACS symptom knowledge[7] or low EMS use for ACS.[10]

## 2.4 Interventions

### 2.4.1 Educational Intervention

The intervention involved delivering the Heart Matters education program to the communities in each LGA. Dedicated HM Coordinators, qualified in relevant fields and familiar with the LGAs, were appointed and received comprehensive training. In the last months of the intervention, when all LGAs had transitioned to the intervention phase, a geotargeted social media campaign (e.g. brief videos on Facebook) was launched in the LGAs.

The educational materials used included Partner resources like the NHFA's Heart Attack Action Plan (available in multiple languages) and program-specific materials such as lived-experience videos and presentation slides. The materials were delivered through various modes (in person or digital, formal or informal) depending on the audience.

### 2.4.2 Control condition

During the control period, no Heart Matters educational activities took place in the trial LGAs.

## 2.5 Outcomes

Outcomes will be examined for adult (aged 18 years or older) residents of the eight LGAs. All outcomes, except survey data, were collected continuously between December 1st 2022 to March 31st 2023 for the main trial and to March 31st 2024 for long-term follow-up. The survey data was collected at three-time points; December 2021-January 2022 (control), August 2022-September 2022 (half-way), April-May 2023 (completion). This Statistical Analysis Plan provides plans for the analysis of the main trial; the analysis of long-term follow-up data will be covered in a subsequent document.

### 2.5.1 Primary outcome

- The primary outcome is EMS use for ACS (the proportion of ACS patients that present to a public emergency department [ED] by EMS[10]). The Victorian Department of Health prospectively collects these data in the Victorian Emergency Minimum Dataset (VEMD).

### **2.5.2 Secondary outcomes**

The following outcomes will be obtained from the Victorian Cardiac Outcomes Registry (VCOR) for ACS patients or ST-elevation myocardial infarction (STEMI) subgroups undergoing reperfusion therapies:

- Patient delay time in STEMI patients (time from symptom onset to decision to seek medical attention; with median delay time to be compared between groups)
- Patient delay within 60 minutes in STEMI patients (the proportion of STEMI patients with patient delay time  $\leq 60$  minutes to be compared between groups)
- Prehospital delay time in ACS patients (symptom onset to arrival at hospital; with median delay time to be compared between groups)
- Prehospital delay time in STEMI patients (symptom onset to arrival at hospital; with median delay time to be compared between groups)
- Prehospital delay within 120 minutes in ACS patients (the proportion of patients with symptom onset to arrival at hospital  $\leq 120$  minutes to be compared between groups)
- Prehospital delay within 120 minutes in STEMI patients (the proportion of patients with symptom onset to arrival at hospital  $\leq 120$  minutes to be compared between groups)

The following outcomes will be obtained from the Victorian EMS STEMI Quality Initiative (VASQI) for suspected STEMI patients transported by EMS:

- Patient delay time in suspected STEMI patients (time from symptom onset to decision to seek medical attention [call ambulance]; with median delay time to be compared between groups)
- Patient delay within 60 minutes in suspected STEMI patients (the proportion of suspected STEMI patients with patient delay time  $\leq 60$  minutes to be compared between groups)
- Prehospital delay time in suspected STEMI patients (symptom onset to arrival at hospital; with median delay time to be compared between groups)
- Prehospital delay within 120 minutes in suspected STEMI patients (the proportion of patients with symptom onset to arrival at hospital  $\leq 120$  minutes to be compared between groups)

The following outcomes will be obtained from online survey data collected in residents of the LGAs August 2021-September 2021, August 2022, and April-May 2023

- Awareness of own risk of heart attack (the proportion who self-report having had a heart risk assessment in last two years to be compared between groups)

- Awareness of heart attack/heart disease as the leading cause of death (the proportion who identify heart attack/disease as a leading cause of death in men/women to be compared between groups)
- Awareness of heart disease (cardiovascular) risk factors (the proportion who correctly identify any cardiovascular risk factor as increasing their risk of heart disease to be compared between groups)
- The number of correctly named heart disease (cardiovascular) risk factors (the mean number of correctly named cardiovascular risk factors to be compared between groups)
- Awareness of heart attack signs and symptoms (the proportion aware of any heart attack symptom[7] to be compared between groups)
- The number of correctly named heart attack signs and symptoms (the mean number of correctly named heart attack symptoms[7] to be compared between groups)
- Confidence in knowing how to act (the proportion very confident/confident about what they would do if experiencing a heart attack to be compared between groups)
- EMS use in severe chest pain scenario (the proportion who state they would call EMS to be compared between groups)
- EMS use in chest discomfort scenario (the proportion who state they would call EMS to be compared between groups)

The following will be obtained from Medicare:

- The number of Heart Health Checks (numbers of Medicare claims for Heart Health Checks, items 699/177) by LGA and month. The number of adults eligible for Medicare in each LGA will allow analysis of this as a rate for each LGA in each month.

The following will be obtained from the VEMD:

- Number of ACS emergency department presentations (numbers of ED presentations that have a final ED diagnosis of ACS[10]), by LGA and month. Adult population sizes of LGAs will be obtained from the Australian Bureau of Statistics to allow analysis of this as a rate for each LGA in each month.
- Number of emergency department presentations that are for unspecified chest pain (the number of ED presentations that have a final ED diagnosis of unspecified chest pain[10]), by LGA and month. Adult population sizes of LGAs will be obtained from the Australian Bureau of Statistics to convert this to a rate for each LGA in each month.
- ACS ED presentations via General Practitioners (the proportion of ACS ED presentations referred to ED by General Practitioners to be compared between groups)

The following will be obtained from the Victorian Department of Health's Victorian Admitted Episodes Dataset (VAED):

- Rates of ACS survival (the proportion of ACS patients surviving to hospital discharge to be compared between groups)

The following will be obtained from the Victorian Cardiac Arrest Registry (VACAR):

- Numbers of patients with an out-of-hospital cardiac arrest by LGA and month. Adult population sizes of LGAs will be obtained from the Australian Bureau of Statistics to convert this to a rate for each LGA in each month.[11]
- Survival to hospital discharge following an out-of-hospital cardiac arrest (proportion of patients with out-of-hospital cardiac arrest surviving to hospital discharge out of all patients with out-of-hospital cardiac arrest to be compared between groups[11])

The following will be collected from the Ambulance Victoria computer-aided dispatch (CAD) records:

- Calls to EMS for chest pain (the proportions of chest pain [event type 10] calls to EMS out of all calls to EMS to be compared between groups [12])
- Calls to EMS for non-chest pain (the rate of non-chest pain [non-event type 10] calls to EMS to be compared between groups; adult population sizes of LGAs will be obtained from the Australian Bureau of Statistics to convert this to a rate for each LGA in each month).

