### Benefits of early treatment and ambulance use for ACS

International guidelines strongly recommend emergency treatment for ACS, which include medication (aspirin and thrombolysis) and procedures (revascularisation) to reopen the blocked blood vessels in the heart (collectively referred to as ‘reperfusion therapies’).

The benefits of reperfusion therapy are maximised when they are administered *within the first 90 minutes following symptom onset (Figure 1)* –these include less heart damage, fewer complications and better short and long-term outcomes.

Reperfusion therapies are not available at every hospital, which is one of the reasons why ambulance use for ACS is recommended internationally.

Paramedics are trained to detect and provide emergency treatment for ACS, and for the potentially life-threatening complications associated with this condition (e.g. cardiac arrest). Transport by ambulance also ensures suspected ACS patients present to hospitals with revascularisation capabilities, and some ambulance services even initiate thrombolysis during transport. Ambulance use is associated with higher rates of reperfusion therapy, the timeliness of its administration, and improved patient outcomes.

*Figure 1. The relationship between time and ACS outcomes.*

**Figure.** Hypothetical Construct of the Relationship Among the Duration of Symptom Acute MI Before Reperfusion Therapy, Mortality Reduction, and Extent of Myocardia

[figure not shown]

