pre-hospital clinical and operational data, and hospital follow-up data. Paramedic suspected STEMI cases are housed in the VASQI with data being drawn from Ambulance Victoria's Communication centre dispatch records, Emergency Medical Services (EMS) patient care records, and from Team Manager review of STEMI cases. Hospital diagnosis, treatment and outcome data for paramedic suspected STEMI cases identified in VASQI are linked from the Victorian Cardiac Outcomes Registry (VCOR) at Monash University and by collaboration with Victorian public hospitals with the capability of performing percutaneous coronary intervention (PCI).

**The Victorian Cardiac Outcomes Registry (VCOR)** is a clinical quality registry that aims to improve the quality of care provided to patients with cardiovascular disease. VCOR is coordinated by Monash University and collects data for all Victorian patients undergoing relevant cardiac procedures. The VCOR collects prehospital, hospital and outcome data.

**Ambulance Victoria keep Electronic Computer Aided Dispatch (CAD)** records for all emergency calls to ambulance. This dataset includes date and chief complaint (e.g. chest pain).

**Medicare** provides access to medical and hospital services for all Australian residents and certain categories of visitors to Australia. The Medicare Benefits Schedule (MBS) list services that are subsidised by the Australian Government under Medicare. Reports can be collated providing anonymised demographic variables on Items in the MBS Schedule. Medicare Items 699 and 177, will support patients to access a heart health assessment through a doctor in a general practice. Reports will be collated on use of these item numbers across local government areas during the intervention period.

**The Heart Foundation's "Heart Watch" Survey** is a quarterly survey conducted using a purposive, non-probability sampling method with quotas for age, gender and area of residence in order to reflect the characteristics of the wider Australian population. Respondents of the survey belong to an online survey panel.

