## 2.7 Research and statistical hypotheses

The primary research hypothesis is that the introduction of the Heart Matters education intervention will lead to an increase in the proportion of ACS patients arriving at the hospital via EMS.

The primary statistical hypotheses are as follows:

- **Null hypothesis:** no difference in the proportion of ACS patients that arrive at the emergency department via EMS will be the same before and after the introduction of the Heart Matters education intervention. That is, the risk difference is equal to 1.

- **Alternative hypothesis (2-sided):** The proportion of ACS patients arriving at the emergency department via EMS will not be the same before and after the introduction of the Heart Matters education intervention. That is, the risk difference is not equal to 1.

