### **3.8.2 Binary outcomes: whether patient delay time $\leq 60$ mins (in STEMI and suspected STEMI patients); whether prehospital delay time $\leq 120$ mins (in STEMI, ACS, and suspected STEMI patients); survival to hospital discharge (in ACS patients); survival to hospital discharge following an out-of-hospital cardiac arrest; acute coronary syndrome emergency department presentations via General Practitioners; calls to EMS for chest pain.**

These binary outcomes will be analysed according to the approach outlined in Section on 3.7.1. Analysis of the survival to hospital discharge following an out-of-hospital cardiac arrest outcome will only include participants who had an out-of-hospital cardiac arrest.

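### Four of the ten delay outcomes are defined only in patients transported by EMS, the behaviour the campaign aims to change, so their comparison can shift through case mix and should be read as conditional on EMS use

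*Supplement*

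**What the plan says.** SAP 2.5.2 lists ten delay outcomes from two registries.

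- **VCOR (six outcomes).** These are taken "for ACS patients or ST-elevation myocardial infarction (STEMI) subgroups undergoing reperfusion therapies": patient delay in STEMI (median, and within 60 minutes), and prehospital delay in ACS and in STEMI (median, and within 120 minutes). No restriction by mode of arrival is stated.
- **VASQI (four outcomes).** The SAP writes: "The following outcomes will be obtained from the Victorian EMS STEMI Quality Initiative (VASQI) for suspected STEMI patients transported by EMS". The four are patient delay and prehospital delay, each as a median and as a proportion within the cut-off. VASQI patient delay is the "time from symptom onset to decision to seek medical attention [call ambulance]; with median delay time to be compared between groups".

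The latest protocol, describing its data sources after Table 3, confirms how cases enter the registry: "Paramedic suspected STEMI cases are housed in the VASQI with data being drawn from Ambulance Victoria's Communication centre dispatch records".

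SAP 2.7 states the primary research hypothesis, that the campaign "will lead to an increase in the proportion of ACS patients arriving at the hospital via EMS".

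For the analysis, SAP 3.8.1 fits quantile regression to the delay times with LGA random intercepts and fixed effects for period and intervention. SAP 3.8.2 says of the binary versions: "These binary outcomes will be analysed according to the approach outlined in Section on 3.7.1". Adjustment for patient characteristics (3.7.3) and subgroup analyses (3.7.4) are specified for the primary outcome only. Nothing in 3.2 or 3.8 tells the reader to interpret the VASQI outcomes differently from the VCOR ones.

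**The concern.** Randomising LGAs to sequences protects a comparison of all patients in a cluster-period. It does not protect a comparison among patients selected by something the intervention may change. Inclusion in the four VASQI outcomes requires transport by EMS, and raising EMS use is the campaign's main aim. Patients who would have come by other means under control, but call an ambulance under intervention, are missing from one side of the comparison and present on the other. Period effects cannot remove this, because the change in case mix follows the intervention and not the calendar.

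The protocol lists reducing delay among its primary objectives. Its section on barriers to ambulance care also describes patient factors linked both to longer delay and to not using an ambulance. So a difference between new and existing EMS users is plausible, although the documents do not quantify it. An intervention coefficient for a VASQI outcome, printed with a confidence interval and p-value, could be taken as the campaign's effect on delay when part or all of it is a change in who is counted.

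**Working it through.** **The plan's own figures.** SAP 2.8 gives 40 ACS patients per LGA per two-month period. With 8 LGAs and 7 analysed periods each (one transition period excluded), 8 x 7 x 40 = 2240, as stated. A stepped-wedge calculation with a random LGA intercept, fixed period effects, ICC 0.09 and the transition cells dropped gives standard errors for the 11-point difference of 0.0396 (baseline variance), 0.0383 (variance at the mean proportion) and 0.0380 (averaged variance). Power is 79.4%, 81.9% and 82.4%, against the stated 80%. These figures concern the primary outcome. The plan gives no sample size or power for any delay outcome.

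**Share of newcomers.** The inputs are 61% and 72% EMS arrival (SAP 2.8, all ACS). Assume that everyone who would use EMS under control also does so under intervention, and that the number of cases is unchanged. Per 100 patients, 61 enter the EMS-only denominator under control and 72 under intervention. The newcomer share is (72 - 61)/72 = 11/72 = 0.153.

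**Shift with every patient's delay held fixed.** Let p_existing and p_new be the shares within 60 minutes among existing and newly transported EMS users.

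Shift = (61 x p_existing + 11 x p_new)/72 - p_existing = 0.153 x (p_new - p_existing).

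The documents give neither share, so both are assumed:

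| p_existing | p_new | Shift in VASQI proportion (points) |
|---|---|---|
| 50% | 10% | -6.1 |
| 50% | 20% | -4.6 |
| 50% | 30% | -3.1 |
| 50% | 40% | -1.5 |
| 50% | 50% | 0.0 |
| 50% | 60% | +1.5 |
| 50% | 70% | +3.1 |
| 60% | 20% | -6.1 |

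**One row in full.** Take p_existing 50%, p_new 30%, and 30% among the 28 patients who never use EMS. The EMS-only proportion goes from 30.5/61 = 50.0% to (30.5 + 3.3)/72 = 46.9%. Across all 100 patients, 30.5 + 3.3 + 8.4 = 42.2 are within 60 minutes under both conditions.

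**Smaller EMS changes.** For p_existing 50% and p_new from 10% to 70%:

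| EMS share | Newcomer share | Range of shift (points) |
|---|---|---|
| 61% to 66% | 5/66 = 7.6% | -3.0 to +1.5 |
| 80% to 85% | 5/85 = 5.9% | -2.4 to +1.2 |
| 80% to 90% | 10/90 = 11.1% | -4.4 to +2.2 |

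**Median patient delay.** Assume lognormal delays with a median of 60 minutes and log-SD 1.2 in existing users. At the 61% to 72% shift, the EMS-only median moves to 66.5 minutes if newcomers' median is twice as long, 70.0 if three times, and 54.2 if half.

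**Table 5 against 2.5.2.** Table 5 has delay rows for patient delay in STEMI and in suspected STEMI, and for prehospital delay in ACS and in suspected STEMI. The two VCOR outcomes for prehospital delay in STEMI have no rows. Of the eight delay outcomes shown, four are VASQI-based, and the only prehospital result specific to STEMI is the EMS-only one.

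**The case against.** The strongest reply is that the plan already handles much of this. The VASQI restriction is declared, Table 5 labels the suspected-STEMI rows separately, and SAP 2.5.2 repeats all four measures in VCOR STEMI patients without restricting arrival mode. That stands. A reader might infer that the trial could report more EMS use but no gain in delay purely because of who is counted. The documents do not support that: six of the ten delay outcomes do not depend on EMS use and are to be analysed alongside.

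The size is also assumption throughout. The 61% and 72% refer to all ACS, and no EMS share for suspected STEMI and no delay distribution by arrival mode is given. Nor do the documents establish that newcomers differ from existing users. This limits the claim to a conditional one of unknown sign, but does not remove it.

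For the two prehospital outcomes, switching to EMS may itself change travel time, so the premise that no delay has changed is clean only for patient delay. That stands too.

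Finally, VCOR has its own selection. It is limited to patients receiving reperfusion, and the protocol states: "Ambulance use is associated with higher rates of reperfusion therapy". The documents do not show that this selection is milder, and do not say how VCOR dates the decision to seek care in patients who did not call an ambulance. VCOR is preferable here because it is not restricted by the primary outcome itself, but it is not free of selection.

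**Conclusion.** The concern holds in conditional form. Four of the ten delay outcomes are restricted to patients selected by a post-exposure behaviour that is the primary outcome, and the planned models do nothing to separate a change in delay from a change in case mix. A shift arises only if the campaign raises EMS use among suspected STEMI patients and the newcomers' delays differ from those of existing users. At the planned all-ACS shift, the effect on the within-60-minute proportion is roughly -6 to +3 points under the assumed shares. It is smaller for smaller EMS changes and zero if delays are equal, and its direction is unknown. The documents do not support saying that the VASQI results will be biased, or biased against the campaign. The primary analysis is unaffected. What is at stake is how secondary results on delay may be interpreted.

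**What to change.** 1. In SAP 2.5.2 and 3.8, state that the four VASQI delay outcomes are descriptive and conditional on EMS transport, and are not estimates of the campaign's effect on delay. They should be read alongside the EMS share and the number of VASQI cases by LGA and period.
2. Base conclusions on delay on the VCOR outcomes, stating that these are conditional on reperfusion and so not free of selection.
3. Add to Table 5 the VCOR STEMI prehospital delay rows (median and within 120 minutes) that 2.5.2 already lists.

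A population rate, such as VCOR STEMI arrivals within 120 minutes per 1,000 adult residents, may look like a way round the problem. It is not recommended. Its denominator is fixed, but its numerator depends on reperfusion, which the campaign may alter through EMS use.

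The cost is SAP wording, a count of VASQI cases by LGA and period, and two added outcomes in Table 5, all from data already planned. The downside is that the VASQI results carry less inferential weight.
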